### Data integrity and management

All data obtained will be kept strictly confidential and will be stored electronically on a database with secured and restricted access. Data transfer will be encrypted and any information capable of identifying individuals will be removed.

### Withdrawal

If a participant withdraws or is removed from the study, the reason and date of discontinuation will be recorded. Any participant who withdraws within year 1 will be asked to have MRI at the end of year 1; participants withdrawing after year 1 will be asked to have MRI on leaving the study.

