### Outcome measures

The co-primary efficacy endpoints of the study will be MRI assessment of volume changes in knee cartilage from baseline to month 24, as well as the Western Ontario and McMaster Universities Index of OA (WOMAC) score 
[31] (Table 
1). The secondary endpoints will be other knee structural changes (cartilage defects, tibial plateau bone area, and bone marrow lesions, meniscal tear and extrusion) from baseline to month 24, and lower limb muscle strength at months 3, 6, 12 and 24 (Table 
1). 

**Table 1 T1:** Timetable and measures to be made

	**Screening**	**Month(s)**				
		**0**	**3**	**6**	**12**	**24**

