**Other measures**						
Core musculature measure		✓			✓	✓
Hand grip strength		✓	✓	✓	✓	✓
Central and upper arm blood pressure		✓		✓	✓	✓
Aortic stiffness		✓		✓	✓	✓
Physical activity (IPAQ)		✓				✓
Body fat		✓			✓	✓
Low foot pain		✓	✓	✓	✓	✓
Low back pain		✓		✓	✓	✓
Depression		✓	✓	✓	✓	✓
Quality of life		✓		✓	✓	✓
Previous knee injury and occupation		✓				✓
Weight		✓	✓	✓	✓	✓
Height		✓				✓
Girth measurements		✓			✓	✓
Knee radiograph	✓					
Serum 25-(OH)D	✓		✓			✓
Serum calcium, phosphate, creatinine	✓		✓			
Sun exposure		✓		✓	✓	✓
Cigarette smoking		✓				✓
Diet (FFQ) and pedometer		✓				✓
Medications	✓	✓	✓	✓	✓	✓
Pill counts and adverse events		✓	✓	✓	✓	✓

Participants who withdraw within one year will be asked to have MRI at month 12; patients who withdraw after one year will be asked to have MRI straight away. MRI: magnetic resonance imaging; WOMAC: Western Ontario McMaster Universities Osteoarthritis Index; 25-(OHD)D: 25-hydroxy-vitamin D; FFQ: food frequency questionnaire.

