### Analysis plan

Statistical primary comparisons for total and subscale WOMAC scores will be made using a repeated measures mixed model with terms for treatment, month, center and the corresponding baseline values as the covariates. The independent *t*-tests will be used to compare changes between groups in quantitative data from baseline to the end of follow-up. Linear regression (annual changes in cartilage volume, cartilage defects, bone area and muscle strength as the dependent variables, and treatment as the independent variable) and logistic regression (development/progression of bone marrow lesions and meniscal abnormalities as the dependent variables, treatment as the independent variable) analyses will be applied in univariate and multivariate modeling adjusted for age, sex, body mass index, baseline 25-(OH)D and other disease status.

In secondary analysis of loss in cartilage volume, the minimal clinically important differences (MCID) in cartilage volume will be calculated 
[47] and logistic regression will be used to determine the association between cartilage loss (> = MCID vs. < MCID) and treatment before and after adjustment for the covariates described above.

Both intention to treat and per protocol analyses will be utilized. Per protocol will be defined as achieving a 25-(OH)D level > 60 nmol/liter at month 3. The last observation carried forward method will be used in the analysis of all outcomes among patients who made at least one follow-up visit but did not complete the whole study.

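### The withdrawal rule asks for an MRI but not for WOMAC, so the pain co-primary of early leavers is left to carried-forward values

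*Protocol article*

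**What the plan says.** The Outcome measures section sets the co-primaries: "The co-primary efficacy endpoints of the study will be MRI assessment of volume changes in knee cartilage from baseline to month 24, as well as"; WOMAC is the second one it names. Table 1 schedules MRI at months 0 and 24, and WOMAC at months 0, 3, 6, 12 and 24.

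The Withdrawal section first requires that "the reason and date of discontinuation will be recorded". It then gives one data-collection rule in two parts: "Any participant who withdraws within year 1 will be asked to have MRI at the end of year 1", and, for those who leave later, "participants withdrawing after year 1 will be asked to have MRI on leaving the study". The footnote to Table 1 repeats it: "Participants who withdraw within one year will be asked to have MRI at month 12; patients who withdraw after one year will be asked to", with an immediate scan requested of the second group. MRI is the only assessment named in either place.

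The Analysis plan says how gaps are filled: "The last observation carried forward method will be used in the analysis of all outcomes among patients who made at least one follow-up visit" without completing the study. It compares WOMAC with a repeated measures mixed model that has month among its terms, and it states that "Both intention to treat and per protocol analyses will be utilized".

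**The concern.** The article addresses withdrawal twice. Each time it secures a follow-up value for one co-primary endpoint and says nothing about the other. Followed as written, the rule recalls an early leaver at month 12, which is already a scheduled WOMAC time point, takes the scan and leaves the pain score to imputation.

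Two things are at stake:

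- **Age of the data.** The WOMAC value that stands for a withdrawn participant can be many months older than the scan from the same person.
- **Participants covered.** Someone who leaves before the first follow-up visit can contribute to the cartilage comparison but have no post-baseline pain score. The two co-primaries could then rest on different sets of randomised participants, which sits poorly with an intention-to-treat analysis.

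If leaving the study is related to pain, and differently so in the two arms, carried-forward scores could distort the WOMAC comparison. A score observed at the recall contact would reduce that exposure at little cost.

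**Working it through.** **Inputs**

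- WOMAC at months 0, 3, 6, 12 and 24; MRI at months 0 and 24 (Table 1).
- MRI after withdrawal: month 12 if the participant leaves in year 1, on leaving if later (Withdrawal; Table 1 footnote).
- Carry-forward for all outcomes, given at least one follow-up visit (Analysis plan).
- 200 per arm, 400 in total, with a 20% dropout allowance (Sample size).

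**The plan's own sample size.** This is reproduced first, to confirm that the dropout allowance is used as stated. For two means, n per arm = 2(1.96 + 0.842)² × SD² / difference².

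- Cartilage volume: 2 × 7.85 × 6.5² / 2.16² gives 143 after rounding up (stated 143).
- Bone area: 2 × 7.85 × 2.8² / 0.9² gives 152 (stated 153).
- Cartilage defects, 80% against 65%: about 137 by the arcsine formula (stated 136).
- Largest stated figure with dropout: 153 / (1 − 0.20) = 191.25, so 192, which 200 per arm covers.

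No stated figure is in dispute, and the fix changes no sample size.

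**Number who could be affected.** 20% × 400 = 80, or 40 per arm. If dropout were 10% to 30% (an assumption, not in the article), the total would be 40 to 120.

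**Age of the last WOMAC at the withdrawal scan.** Gap = month of scan − month of last scheduled WOMAC attended.

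| Leaves | MRI requested | Last scheduled WOMAC | Gap |
|---|---|---|---|
| Before month 3 | Month 12 | Month 0 (baseline only) | No post-baseline score |
| After month 3, before month 6 | Month 12 | Month 3 | 12 − 3 = 9 months |
| After month 6, before month 12 | Month 12 | Month 6 | 12 − 6 = 6 months |
| Late in year 2 | On leaving | Month 12 | Approaching 24 − 12 = 12 months |

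In the second row, carrying forward to month 24 makes a month-3 score stand for a value 24 − 3 = 21 months later.

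In the first row, the carry-forward rule offers no remedy. It requires a follow-up visit, and even if the recall for the scan counted as one, there would be no post-baseline WOMAC to carry.

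**Information at month 24.** If carried-forward values are not counted as information, 200 × 0.80 = 160 per arm have an observed WOMAC. The standardised difference detectable with 80% power is √(2/n) × (1.96 + 0.842):

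- n = 200: 0.280
- n = 160: 0.313

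This is a bounding illustration, because a mixed model also uses the scores observed before withdrawal.

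**The case against.** The strongest case on the other side has four parts.

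**An MRI timing rule does not exclude other assessments.** MRI needs a special rule because it is otherwise done only at months 0 and 24, whereas WOMAC has three visits before month 24. A condensed article may leave other withdrawal procedures to the full protocol. This explains why MRI is mentioned. It does not remove the uneven treatment: the article states a specific collection rule twice, and as stated the rule covers one co-primary of two.

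**The mixed model already uses every score before withdrawal.** That is so, and it limits the loss. It does not help the participant with no post-baseline score, and the Analysis plan applies carry-forward to all outcomes.

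**The size is easily overstated.** This stands. Eighty is the planning allowance for dropout. Some leavers will decline the recall and others will leave soon after a visit. The gap of nearly 12 months arises because nobody has a visit between months 12 and 24.

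**The fix is more than a sentence.** This stands in part. These people have left the study, so any further assessment needs their agreement, and the article does not say that the scan takes place at a clinic visit with staff present. Recruitment is under way, and the Quality assurance section says that protocols will stay unchanged during the study.

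A reader might also infer a safety failing: that safety bloods are withheld from leavers and that adverse-event collection stops when they leave. The article does not support this. Calcium, phosphate and creatinine are scheduled for nobody after month 3, so none is due at a later scan. Table 1 lists "Pill counts and adverse events" at each visit from month 0, but the Safety assessments section also has spontaneous reports recorded throughout the study, and the reason for leaving is recorded. The most that can be said is that no adverse-event enquiry is named at the recall contact.

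Nor does the article show that leavers mostly stop for harm or lack of effect. It gives no withdrawal reasons and no rates by arm.

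**Conclusion.** The point holds for WOMAC. The withdrawal rule, stated in the Withdrawal section and in the Table 1 footnote, requests MRI without WOMAC and so leaves later pain scores, a co-primary endpoint, to carry-forward. The last score can be 9 months older than the scan for someone last seen at month 3, nearly 12 months older for someone leaving late in year 2, and absent after baseline for someone leaving before month 3.

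At most about 80 of 400 participants are affected at the planned 20% dropout. Bias in the WOMAC comparison is a risk whose direction and size cannot be derived from the article. The conclusion assumes that the rule is followed as written and that the fuller protocol does not already add WOMAC at this contact. It is a correction worth making, and it does not undermine the design.

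**What to change.** In the Withdrawal section and the Table 1 footnote, ask withdrawing participants to complete WOMAC at the same contact as the MRI, where they agree. As a questionnaire, it could be completed even if the scan is done away from the study clinic.

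In the Analysis plan, use a WOMAC score taken at the month-12 recall as the month-12 observation in the mixed model. Enter scores taken on leaving after year 1 at their actual time. Both replace a carried-forward value. Because the model has a month term, the plan should say how off-schedule scores are placed.

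A brief adverse-event enquiry at the same contact is optional. No added blood sampling is needed.

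The cost is a few extra minutes at a contact already requested, which some participants may decline, and a documented change to a protocol that is already recruiting. The sample size is unaffected.

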### Monitoring

The trial will be overseen and monitored by a project manager. The project manager will visit each site to examine trial procedures to ensure data quality and compliance with the trial protocol.

## Discussion

We have proposed this protocol to determine if vitamin D supplementation can slow disease progression in patients with knee OA. Vitamin D may have beneficial effects for the treatment of OA, although there are currently no recommended guidelines for this approach 
[48]. Hence, well-designed randomized controlled trials are required to test if vitamin D has disease-modifying and pain-relieving effects. Such studies also need an appropriate follow-up period to capture joint structural changes using objective measurements over the course of OA, and this has been incorporated into the design of the VIDEO study.

Assessing disease-modifying effects on OA requires an accurate measurement tool that is able to evaluate improvements in cartilage and joint health. Radiographic assessment of OA is two-dimensional, lacks sensitivity for changes over a short period and is highly susceptible to measurement error through factors such as variation in joint positioning 
[49]. MRI allows direct, accurate and reliable assessment of joint structural changes over time. These structural changes include cartilage loss, cartilage defects, increased tibial bone area, subchondral bone marrow lesions, meniscal tears and meniscal extrusion. Almost all these structural changes are predictive of total knee replacement 
[45,50,51], suggesting they are clinically relevant. Simultaneously, we will assess change in knee pain over time using WOMAC as a co-primary endpoint. Thus, the findings from this study will show whether vitamin D supplementation has both disease-modifying and symptom-relieving effects.

As suggested by the 2011 Endocrine Society Clinical Practice Guideline, all adults aged 50 to 70 years, and those over 70 years old require at least 600 and 800 IU/d of vitamin D respectively, to maximize bone health and muscle function. To raise blood levels of 25-(OH)D above 75 nmol/liter (the lowest sufficient threshold) requires at least 1500 to 2000 IU/d of supplemental vitamin D 
[52]. Thus, our study design provides a dose of 50,000 IU monthly to achieve serum 25-(OH)D levels above 60 nmol/liter in all compliant subjects 
[53]. This method will be less costly and will be more convenient than daily treatment. Toxicity is extremely unlikely with this dose.

Two sub-studies will simultaneously be included in this trial. Firstly, we will examine the effects of vitamin D on the function of the deep lumbo-pelvic stabilizing muscles. Besides implications for low back pain, in healthy people core muscles have also been implicated in varying aspects of physical function. The lateral abdominal muscles are theorized to control movement and provide stability to the trunk for functional activities and this is supported in a number of studies 
[54]. Vitamin D supplementation may have beneficial effects on functionally important core muscles. Secondly, we will determine the effect of vitamin D supplementation on blood pressure and aortic stiffness. A recent systematic review suggested that there is accumulating evidence to support the hypothesis that vitamin D deficiency contributes to hypertension, and randomized controlled trials (RCTs) are greatly needed to clarify and to definitively prove the effect of vitamin D on blood pressure 
[55]. The VIDEO study aims to be the first to assess this.

In summary, knee OA is a major, but poorly understood, public health problem. Vitamin D deficiency may play a role in the progression of OA, and based on our novel preliminary data, the VIDEO study has been designed to determine whether intervening with vitamin D supplementation can in fact slow the progression of this disease and relieve knee pain. If correcting vitamin D deficiency can reduce rates of cartilage loss to lower levels as seen in older people without OA, it will significantly prolong the time it takes to reach end-stage OA eventually requiring joint replacement. This suggests great potential for substantial cost savings through reductions in joint replacement surgery, as well as potential for great improvements in the quality of life for people with OA. The success of this study will provide scientific evidence for using a cost-effective and innovative approach to addressing this clinically significant problem and will lend itself to an easy public health intervention.

## Trial status

Upon submission, VIDEO study is in the process of patient recruitment.

## Abbreviations

25-(OH)D: 25-hydroxy-vitamin D; ACR: American College of Rheumatology; AQOL: assessment of quality of life; BIA: bioelectrical impedance analysis; CRF: case report form; FSEL: fast spin echo; FFQ: food frequency questionnaire; GRE: gradient echo; ICC: interclass correlation coefficient; IPAQ: International Physical Activity Questionnaire; LM: lumbar multifidus; MCID: minimal clinically important differences; MMP: metalloproteinase; MRI: magnetic resonance imaging; OA: osteoarthritis; OARSI: Osteoarthritis Research Society International; PHQ-9: Personal Health Questionnaire Depression Scale-9; PGE_2_: prostaglandin E_2_; RAAS: renin-angiotensin-aldosterone system; RCT: randomized controlled trial; SOP, standard operating procedure; TASOAC, Tasmania Older Adult Cohort; TrAb: transversus abdominus; VAS: visual analogue scales; VIDEO: Vitamin D Effects on Osteoarthritis; VDR: vitamin D receptors; WOMAC: Western Ontario McMaster Universities Osteoarthritis Index.

